# SUMMARY/SYNOPSIS

| The acute effects of chlorogenic acid on cognitive function  and mood in healthy older adults | | | | | |
| --- | --- | --- | --- | --- | --- |
| *Principal Investigator:* [name] | | | | | |
| *Study center(s):* Swinburne University of Technology, Melbourne, Australia | | | | | |
| *Objectives:* The primary objective is to evaluate whether an acute dose of chlorogenic acid (CGA) improves cognitive function and mood in healthy older adults.  Secondary objectives are to:   1. Evaluate whether it is the CGAs found in decaffeinated coffee that are attributed to the cognitive and mood enhancing effects; 2. Replicate the positive acute effects of 6 grams decaffeinated coffee on attention and mood; 3. Evaluate whether an acute dose of CGA and decaffeinated coffee improves cerebral blood flow, and whether modulations to cerebral blood flow are associated with CGA/decaffeinated coffee-related modulations to cognitive performance and mood | | | | | |
| *Outcome:*  *Primary outcome measure: Attention*  Rapid visual information processing task (accuracy) - measure of sustained attention. This task also loads heavily on working memory.  *Secondary outcome measures:*  *Other cognitive tests*   - Rapid visual information processing task (as above) - reaction time and false alarm rate - Inspection Time task - measure of visual information processing speed - Serial sevens - measure of concentration and working memory - Serial Threes - measure of concentration and working memory - Jenson Box reaction time task – measure of reaction time performance whereby decision time and movement time are separated - N-back task – measure of sustained and selective attention and impulsivity - Emotional face recognition task - measure of emotional processing and attention   *Mood scales*   - Bond & Lader Visual Analogue Scales (Bond & Lader, 1974) – subjective measure of mood and alertness - Caffeine Research Visual Analogue Scales - subjective assessment of feelings of "relaxed", "alert", "jittery", "tired", "tense", "headache", overall mood", and "mental fatigue".   *Other*   - - Brain blood doppler flow   Cognitive performance and mood will be assessed at baseline, 40 minutes and 120 minutes post treatment consumption. Brain blood doppler flow will be measured at baseline and 90 minutes post treatment consumption. Blood samples will be obtained at baseline (training session day), 10 minutes, 90 minutes, and 160 minutes post treatment consumption for bioavailability analyses.  Note: outcome measures that were found to be modulated with the specially processed decaffeinated coffee in the previous acute clinical trial will be administered in the present study. | | | | | |
| *Design:* This is an acute cross-over, placebo-controlled, double blind, randomized, single centre, clinical trial with three treatment conditions: chlorogenic acid, decaffeinated coffee and placebo. | | | | | |
| *Number of patients(to be enrolled / to be analysed):* 66/58 healthy older adults | | | | | |
| *Description of subjects and main criteria for inclusion:* Healthy older adults (male and female) aged 50+. Participants must be light to moderate coffee drinkers (i.e. with caffeine), where subjects drink no more than 8 cups of coffee a week. No existing or pre-existing physical or neurological conditions, no history of psychiatric, cardiac, endocrine, gastrointestinal, or bleeding disorders, not taking any medication that could potentially affect the outcome of the study (i.e. psychoactive medication) including drugs, excessive amounts of alcohol, non-smokers, not on a potassium reduced diet, not under treatment with spironolactone-like anti-diuretics, aldosteron-receptors antagonists or angiotensin II- antagonists and no food allergies. | | | | | |
| *Product(s) to be tested:*  Chlorogenic acid in placebo matrix (maltodextrin and CHE mixed with coffee flavour and colour); decaffeinated coffee; and placebo (maltodextrin and CHE mixed with coffee flavour and colour). | | | | | |
| *Amount, dosage, route of administration, duration of treatment:* - 540 mg chlorogenic acid mixed in a placebo matrix (5460mg maltodextrin and CHE mixed with coffee flavour and colour). The CGA is equivalent to the level found in 3 servings of a specially processed decaffeinated coffee (the chlorogenic acid will contain a similar profile to the specially processed decaffeinated coffee administered in the acute study);   - decaffeinated coffee (6g); - placebo (6 g maltodextrin and CHE based with coffee flavour, colour and aroma).   All treatments will be administered orally as a hot coffee beverage which must be drunk within 15 minutes. Participants will consume each of the coffee beverages on separate testing days. Experimental testing sessions will be separated by at least a one week washout period. | | | | | |
| ***Study plan:*** | **V0** | **V1** | **V2** | **V3** |  |
| *Weeks* | 0  Training session | 2 | 3 | 4 |  |
| Informed consent | X |  |  |  |  |
| History / subjects data | X |  |  |  |  |
| Cognitive tests | X | X | X | X |  |
| Subjective ratings | X | x | X | X |  |
| Brain Doppler blood flow |  | x | x | x |  |
| Blood sampling | X | x | x | x |  |
| Treatment |  | x | x | x |  |
| Safety assessment | X | x | x | x |  |

# INTRODUCTION

Coffee is one of the most widely consumed beverages throughout the world. The physiological and behavioural effects of coffee (with caffeine) have been extensively studied over the past four decades. Research has generally shown caffeine to exert positive effects on cognitive performance such as reaction time, alertness, and vigilance (Haskell et al., 2005, 2008; Smit & Rogers, 2000; Frewer & Lader, 1991; Lieberman et al., 1987; Swift & Tiplady, 1988; Lorist et al., 1995; Rees et al., 1999).

Previous research has focused on the effects of caffeine on cognition, and coffee is only a source of caffeine. Coffee is not only caffeine. Coffee contains many other compounds, such as chlorogenic acids, caffeic acid, and ferulic acid, which are known to exert powerful antioxidant properties (Natella et al., 2002; Pellegrini et al., 2003; Olthof et al., 2001; Nardini et al., 2002; Yu et al., 2006). As caffeine exerts significant effects on the brain (Kenemans & Lorist, 1995; Ruijter et al., 2000), the potential beneficial effects of non-caffeine constituents in coffee are poorly understood. Furthermore, as the effects of non-caffeine compounds may modulate or even oppose those of caffeine (de Paulis & Martin, 2004), the acute effects of other compounds found in coffee are difficult to observe, except in decaffeinated coffee.

In a recent trial conducted by Swinburne University and Nestlé, it was found that 3 servings of regular decaffeinated coffee had little or no effect on cognitive function and mood in a healthy older population, thus suggesting that coffee compounds found in regular coffee do not modulate cognitive function or mood. However, the results did indicate that 3 servings of a specially processed decaffeinated coffee exerted positive trend-level acute effects on cognition (specifically attention) and mood (increasing alertness and relaxation, and decreasing reports of mental fatigue and headaches). These findings suggest that there are compounds (other than caffeine) in this specially processed decaffeinated coffee that appear to have positive effects on cognitive function and mood that are not found or that are not at the same level as that found in regular coffee. As chlorogenic acids (CGA) are the most abundant family of compounds found in this specially processed decaffeinated coffee, it is possible that the positive cognitive and mood effects observed are attributed to the chlorogenic acids. To further explore this possibility, the present study aims to assess the effect of pure chlorogenic acid on cognitive function and mood in a healthy older population. The chlorogenic acid will be derived from coffee and the dose to be administered will be the same as is found in 6g of this specially processed decaffeinated coffee. To further understand whether it is the CGAs in the specially processed decaffeinated coffee that are attributed to the positive effects, a second aim is to compare the effects of pure CGA with the decaffeinated coffee. If it is the CGAs contributing to the positive effects, it is expected that there should be no difference in cognitive performance and mood between pure CGA and decaffeinated coffee.

Finally, as the results from the initial acute clinical trial are the first indication that a non-caffeinated pure coffee may improve cognitive performance, the study findings need to be replicated and confirmed. Thus, the third aim is to replicate and confirm the previous trend-level findings and show that 6g decaffeinated coffee improves attention and mood in a healthy older population.

# OBJECTIVES OF THE TRIAL

## 3.1 Main objective

The primary objective is to evaluate whether an acute dose of CGA improves cognitive function and mood in healthy older adults.

Cognitive function will be assessed with a battery of standard validated behavioural cognitive tests. Cognitive functions assessed will be attention, working memory, emotional attention, information processing speed, and reaction time performance.

## 3.2 Secondary objectives

The secondary objectives of the research project are:

- Evaluate whether it is the CGAs found in decaffeinated coffee that are attributed to the cognitive and mood enhancing effects;
- Replicate and extend the positive acute effects of 6 grams decaffeinated coffee on attention and mood
- Evaluate whether an acute dose of CGA and decaffeinated coffee improves cerebral blood flow and whether modulations to cerebral blood flow are associated with CGA/decaffeinated coffee-related modulations to cognitive performance and mood

# TRIAL DESIGN

## 4.1 Type of trial

The proposed study is an acute, cross-over, double blind, counter-balanced, placebo-controlled, randomized, single centre, clinical trial with 3 treatments: CGA, decaffeinated coffee, and placebo.

## 4.2 Subjects, groups and centres

The number of subjects to complete the study protocol will be 58 (see 9.3 statistical section). All subjects will complete the 3 treatment conditions. Subject recruitment will be 66 to provide for a 10% drop-out rate.

The study will be a single-centred study, where all data will be collected at the Brain Sciences Institute, Swinburne University, Melbourne, Australia.

## 4.3 Duration of subject participation

The duration of the subject participation will be 3 weeks. Subjects will be tested on three different test days, separated by at least a 1 week washout period. Each experimental session will take approximately 4 hours to complete. Prior to the experimental testing sessions, subjects will undergo one separate training session (approximately 1 hour).

# Study population

## 5.1 Description

Healthy older male and female adults aged 50+ will be eligible to participate in the study.

## 5.2 Subject inclusion criteria

All subjects must comply with all the following inclusion criteria:

- Age 50 and over
- Healthy (i.e. absence of all exclusion criteria) older male and female adults
- Light to moderate coffee drinkers (i.e. with caffeine)
- Drink no more than 16 cups of coffee per week
- Participants must abstain from caffeine-containing foods and beverages, alcohol, no foods containing chlorogenic acids, and only food with low polyphenol content for 24 hours prior to the training session and each testing session.
- Written informed consent obtained

## 5.3 Subject exclusion criteria

Subjects representing one or more of the following criteria are excluded from participation in the study.

- Existing or pre-existing physical or neurological conditions
- History of psychiatric, cardiac, endocrine, gastrointestinal, or bleeding disorders
- Clinically high blood pressure
- Under treatment with spironolactone-like anti-diuretics, aldosteron-receptors antagonists or angiotensin II- antagonists
- Hearing impairment
- Psychoactive medications
- History of substance abuse
- Smoker
- Food allergies
- Potassium reduced diet
- Score <24 on the Mini-Mental State Exam
- Currently participating or having participated in another clinical trial during the last 2 months prior to the beginning of this study

# TREATMENT OF SUBJECTS

## 6.1 Product description

The CGA will be manufactured at Nestlé Product Technology Centre (PTC) in Orbe, Switzerland. The CGA is derived from coffee beans. The instant decaffeinated coffee is non-commercial and will also be manufactured by PTC Orbe. The placebo (also produced in PTC Orbe) will consist of a small dose of maltodextrin and CHE (soluble powder made from rice cereal) mixed with coffee flavour and colour. The placebo will also be used as the coffee matrix for the CGA condition.

### Composition

The instant decaffeinated coffee is made from a mixture of roasted and green beans. The CGA is derived from green coffee beans.

Products to be tested:

- 540mg Chlorogenic acid mixed with placebo (maltodextrin and CHE (soluble powder made from rice cereal) mixed with coffee flavour and colour)

- 6 g decaffeinated instant coffee derived from green and medium roasted beans

- Placebo (maltodextrin and CHE (soluble powder made from rice cereal) mixed with coffee flavour and colour)

Potassium will be added at very small doses during the extraction process of the CGA. Therefore, subjects on a reduced potassium diet should be excluded.

### Form and dosage

All products will be in powder form.

Instructions for correct preparation will be printed on the label in English.

All coffee treatments will be dissolved and administered as a normal hot coffee drink. Prior to administration, one coffee sachet (6g) will be dissolved in 300 ml boiled water. Milk and sacchran can be added by participants to suit their own taste.

### Quality control

Quality control will be performed by Nestlé at the production stage/on product release, at the end of data collection, and at other times as deemed necessary. The expiry date of the product is marked on the packaging.

### Packaging and labeling

Coffee treatments will be packaged into individual sachets for each separate testing session. Each sachet will be labelled with the study protocol number (10.09.NRC), treatment code (A, B, or C), storage conditions, preparation instructions, and expiry date (See Appendix 1 for treatment label).

### Blinding technique

All products will be blinded by PTC Orbe. The products will be labelled with the trial number (10.09.NRC), and will be distinguishable by the letter printed on the label (i.e. A, B, or C). The identity of the specific product will be blind to subjects, support staff, investigators and the clinical project manager. The code will only be known by the manufacturer. A code break envelope will be supplied to the study site so that the code may be broken in case of emergency.

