## Treatment administration

### 6.2.1 Amount, dose, concentration, frequency

Subjects will receive equivalent of 3 servings of coffee (one of the three study treatment conditions) immediately after baseline testing is completed. Subjects will consume the coffee orally within 15 minutes. In total, each subject will complete three treatment conditions: CGA (540mg CGA mixed in 5460mg placebo matrix;) instant decaffeinated coffee (6 grams); and placebo (6 grams maltodextrin and CHE mixed with coffee flavour and colour). The coffee beverage will be prepared by the investigator at the study site. Milk and sacchran can be added by participants to suit their own taste. Note that in a previous pharmacokinetic study conducted at Nestlé, no modulations to the bioavailability of Nescafé PROTECT was found when black coffee was mixed with milk (Renouf et al., 2008).

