## 8.9 Breaking of the code

The investigator will receive one sealed envelope containing the product identification to be opened only in case of medical emergency.

In circumstances where the investigator identifies an urgent need to break the code, the Clinical Project Manager or the Project Leader should be contacted. All attempts to avoid breaking the code (i.e. withdrawal of treatment) should be made. The code break envelope may be used by the investigator directly in true emergencies. In such cases, the rationale must be documented on the corresponding envelope, with immediate notification of the Clinical Project Manager or the Project Leader.

The code break will also be reported in the subject specific case report form (CRF) and events leading to the emergency breaking will be recorded in the serious adverse event (SAE) report form. All envelopes will be retrieved at the end of the study.

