## 9.4 Randomization

The products used in this study will be coded (A, B and C). A randomization schedule will be generated using Williams Design in R 2.6.1 using these codes. The randomization schedule will be made available to the investigator by hard copy.

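### One fixed letter per product and a single code-break envelope turn any emergency unblinding of one subject into unblinding of site staff for the whole trial

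*Protocol*

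**What the plan says.** The arrangement is spread over several sections of the Protocol.

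- **Coding.** Under Blinding technique the products "will be distinguishable by the letter printed on the label (i.e. A, B, or C"). Under Packaging and labeling the sachet carries the study number and "treatment code (A, B, or C), storage conditions, preparation instructions, and expiry date"; no subject or kit number is listed. Appendix 1 shows only three labels, 1009-A, 1009-B and 1009-C.
- **Schedule.** Section 9.4 builds the Williams design on the same codes ("The products used in this study will be coded (A, B and C") and adds: "The randomization schedule will be made available to the investigator by hard copy".
- **Preparation.** Section 6.2.1: "The coffee beverage will be prepared by the investigator at the study site". Section 6.4.1 also gives day-to-day dispensing to the investigator.
- **Code break.** Section 8.9: "The investigator will receive one sealed envelope containing the product identification to be opened only in case of medical emergency". The sponsor's clinical project manager or project leader should be contacted first, but "The code break envelope may be used by the investigator directly in true emergencies".
- **Who must stay blind.** Blinding technique: "The identity of the specific product will be blind to subjects, support staff, investigators and the clinical project manager". The same paragraph reserves knowledge of the code to the manufacturer.

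**The concern.** Each letter means the same product in every subject, so what staff learn about a letter in one subject applies to all the others. The person who must stay blind also holds the list of letters for all subjects, handles the lettered sachets, and keeps the only key. The envelope contains the key itself, not one subject's allocation, so the Protocol has no way to unblind one subject and leave the rest masked.

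At stake is the conduct of the sessions still to be run and the handling of data already collected. Several outcomes are open to influence by someone who knows the product. The mood scales are self-rated. Inspection Time and Doppler results are written directly into the case report form (section 8.10.1). All the cognitive tests depend on effort and so on encouragement. Once the key is known on site, it cannot be hidden again for the remaining subjects.

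**Working it through.** The Protocol gives no figure for this, so there is none to reproduce. The check counts how many subject-sessions each kind of disclosure identifies.

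**Inputs**
- Subjects to be enrolled: 66 (section 4.2).
- Treatments per subject: 3, all taken by each subject (section 4.2).
- Letters: 3, one per product, common to all subjects (Packaging and labeling; Blinding technique; Appendix 1).
- Letter given to each subject at each visit: known on site from the schedule (section 9.4).

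**Step 1. Total sessions.** 66 x 3 = 198.

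**Step 2. Uncertainty before any disclosure.** Three products can be assigned to three letters in 3! = 6 ways. The schedule alone rules out none of the six, so holding it does not by itself reveal any product.

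**Step 3. The envelope is opened.** One of the six assignments remains. Combined with the schedule, it identifies 198 of 198 sessions (100%), including those already completed. The emergency concerned one subject, who accounts for 3 of 198 = 1.5%.

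**Step 4. One letter is correctly identified without the envelope.** Two assignments remain. Each subject receives that letter once, so 66 of 198 sessions (33%) are identified. With nothing else known, the other two products stay at 50:50.

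**Step 5. Two letters are correctly identified.** One assignment remains, and all 198 sessions are identified.

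**Step 6. Which comparisons step 4 touches.** CGA and placebo share the same maltodextrin and rice-cereal matrix (section 6.1), while the third product is real instant coffee. If the letter recognised is the coffee, both comparisons involving decaffeinated coffee are exposed. CGA versus placebo, the primary comparison, is not.

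| Disclosure | Assignments left | Sessions identified |
|---|---|---|
| None | 6 | 0 of 198 |
| One letter | 2 | 66 of 198 (33%) |
| Two letters, or the envelope | 1 | 198 of 198 (100%) |
| Envelope, if codes and envelopes were subject-specific | not applicable | 3 of 198 (1.5%) |

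**The case against.** The case for leaving the scheme alone has real substance.

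- **A code break is unlikely.** The subjects are healthy, each product is a single supervised drink, and section 8.9 asks staff to try to avoid breaking the code, to contact the sponsor and to record the reason. This stands. It lowers the probability of the event, but not its reach.
- **The investigator needs to know which letter to give.** This is true under letter coding, and the schedule reveals no product by itself. The exposure comes from the schedule together with the key.
- **The primary outcome is well protected.** RVIP hits are button presses, and section 8.10.2 does not list RVIP among the tests excepted from automatic recording. No rater scores them, so any bias would have to come through instruction or encouragement.
- **Section 8.9 refers to envelopes in the plural and to a subject-specific case report form.** Neither describes subject-level envelopes, and the same section says there is one envelope.

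A reader might also infer more than the Protocol supports:

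- **That one correct guess unblinds the whole trial.** It does not; steps 4 and 6 show its limit.
- **That the products can be told apart by look or smell.** The Protocol does not say so. The synopsis describes a placebo with coffee flavour, colour and aroma.
- **That those who prepare the drinks also run the tests.** The Protocol does not say who administers them.
- **That the blind review in section 9.5 would see data grouped by letter.** The Protocol says only that blinded data are used. How that dataset is prepared may be settled in an analysis plan that is not shown.

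**Conclusion.** The point holds for the code-break route and needs no assumption about taste or appearance. As written, unblinding one subject reveals to site staff the product in up to 198 sessions instead of 3. The figure assumes that all 66 subjects enrol and complete three sessions.

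The second route, letter-based inference, is conditional. If staff correctly identify one letter, that product is known in all 66 subjects and the other two remain undetermined. Whether such identification is feasible is not stated.

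In both cases it is staff who are exposed. Nothing in the Protocol passes the key to subjects. The likely harm is greatest for self-rated mood and manually recorded outcomes, and for test encouragement, and least for the computer-recorded RVIP count. Knowledge gained late cannot alter how completed sessions were run, though it can affect how their data are handled. This is an avoidable weakness in design, worth correcting because the remedy is cheap before the first subject and unavailable after a code break. An analysis plan cannot repair it, because labelling, custody of the schedule and the form of the envelope are all fixed in the Protocol.

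**What to change.** Amend Packaging and labeling, Blinding technique, section 8.9, section 9.4 and Appendix 1 together:

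1. Label each sachet with subject number and visit, 66 x 3 = 198 labels, with no product letter.
2. Keep the product sequence list with the manufacturer or an independent statistician. The investigator then needs no schedule, because the label shows which sachet to use.
3. Supply one sealed code-break envelope per subject, 66 in all, each disclosing that subject's products only.

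The cost is 198 individual labels in place of three designs, 66 envelopes in place of one, and the packing work at the manufacturer. Sachets are already packed singly for each session, so the packaging format need not change. Sachets also cease to be interchangeable between subjects, so any spares need subject-and-visit labels too.

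The change confines a code break to 3 of 198 sessions and stops inference from one subject's letter to another's. It does not stop staff recognising a product by look or smell when they open a sachet, if the products do differ in that way.
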